## Abstract

**Background:**

Tuberculosis (TB) remains a significant public health challenge, particularly in low- and middle-income countries (LMICs) such as Pakistan, where TB and depression frequently co-occur, negatively impacting treatment adherence and outcomes. The cognitive therapy for depression in tuberculosis (CONTROL) trial evaluates the effectiveness of a cognitive behavioral therapy (CBT)-based intervention integrated into TB care. Following the Proctor’s framework, this process evaluation aims to assess key implementation outcomes of the trial, including acceptability, adoption, feasibility, appropriateness, fidelity, penetration, and sustainability, to inform the potential scale-up of the intervention within Pakistan’s routine TB care.

**Methods:**

This mixed-methods process evaluation is embedded within the CONTROL randomized controlled trial conducted in Khyber Pakhtunkhwa, Pakistan. Quantitative data collection will include structured implementation outcome measures such as Intervention Appropriateness Measure (IAM), Acceptability of Intervention Measure (AIM), Feasibility of Intervention Measure (FIM), Applied Mental Health Research (AMHR) group tool, Revised Cognitive Therapy Scale (CTS-R), CBT-content delivery assessment checklist, Client Service Receipt Inventory (CSRI), and trial administrative data logs. Qualitative data will comprise semi-structured interviews and focus group discussions. Data collection will be at three points: 8-, 24-, and 32-week post-randomization across 12 TB care facilities. Quantitative data will be analyzed descriptively, while qualitative data will be analyzed thematically, followed by triangulation of findings.

**Discussion:**

The process evaluation will inform the implementation of CBT-based intervention within TB care. It will also identify barriers and facilitators for integrating mental health care in the TB control program for future scale-up. Findings will inform policymakers on the feasibility of incorporating mental health interventions into routine TB care, support improved patient outcomes, and contribute to global implementation science on integrated mental health care for chronic diseases.

**Trial registration:**

ISRCTN10761003. Registered on November 2023.

## Introduction

Tuberculosis (TB) continues to be one of the leading causes of death worldwide, posing a significant public health challenge. Despite advancements in diagnostics, treatment protocols, and global TB control strategies, the disease remains a burden, especially in low- and middle-income countries (LMICs). According to the World Health Organization (WHO) 2024 report, approximately 10.8 million people contracted TB in 2023, with 1.25 million deaths attributed to the disease [1]. Over 95% of these cases and deaths occur in LMICs, where health systems often struggle to provide consistent care due to resource constraints, socio-political challenges, and competing healthcare priorities [2].

Pakistan ranks among the top five high-burden countries for TB, contributing significantly to global morbidity and mortality [2]. The country also has one of the highest rates of multidrug-resistant TB (MDR-TB), further complicating TB control efforts. Annually, Pakistan reports over 500,000 new TB cases [2], with a substantial proportion facing treatment interruptions due to socioeconomic barriers, stigma, and limited access to care. TB imposes profound economic, social, and psychological impacts on affected individuals and their families, often exacerbating the cycle of poverty and illness [3].

Beyond its direct physical health implications, TB frequently co-occurs with mental health disorders, particularly depression and anxiety [4]. These psychological conditions are prevalent among TB patients, with studies estimating that up to 50% of patients experience depressive symptoms during their treatment [5]. Poor mental health can negatively impact TB outcomes through various pathways related to the disease. This bidirectional relationship between TB and mental health creates a complex interplay: the physical and social burdens of TB can trigger or exacerbate mental health issues, while depression and anxiety impair adherence to anti-TB treatment (ATT), increasing the risk of treatment failure and worsening clinical outcomes [6].

Despite ample evidence, mental health care remains a neglected component of TB control programs globally, including in Pakistan [7]. TB control efforts primarily focus on detecting and treating the infection, often overlooking the psychological needs of patients [8]. This gap in care highlights an urgent need for integrated approaches that address both the physical and mental health aspects of TB. Such integration can improve patient outcomes and align with global health priorities, emphasizing holistic, patient-centered care models [9].

Integrating mental health interventions into routine TB care has shown promise in improving both TB and mental health outcomes [7]. Cognitive behavioral therapy (CBT), an evidence-based approach to managing depression and anxiety, has demonstrated effectiveness in reducing depressive symptoms and enhancing adherence to medical treatment [10, 11]. In LMICs, task-sharing approaches—where non-specialist health workers are trained to deliver these interventions—have emerged as a practical and scalable solution [12]. These approaches leverage existing healthcare infrastructure and address workforce limitations by enabling lay health workers to provide mental health care under supervision [13]. Task-sharing has been successfully implemented in other disease contexts, showing potential for adaptation in TB care programs [14].

### A brief overview of the trial

The COgNitive Therapy for depRessiOn in tubercuLosis treatment (CONTROL) trial aims to address the dual burden of TB and depression in Pakistan [15]. It is a pragmatic parallel arm (intervention and control arm), randomized controlled trial (RCT) conducted across TB treatment centers in Khyber Pakhtunkhwa (KP), Pakistan, evaluating the clinical and cost-effectiveness of CONTROL intervention in a randomised controlled trial [15]. In these TB centers, the program is implemented through the Directly Observed Therapy Short Course (DOTS) strategy, ensuring structured service delivery to patients. The CONTROL CBT-based intervention aims to improve the outcomes both for depression and TB in people with TB and MDR-TB. The trial tests its effectiveness and cost-effectiveness and examines how the intervention can be implemented in the real-world setting of the Provincial TB Control Programme, KP (PTP-KP) in Pakistan [15]. Patients in the intervention arm receive both Enhanced Treatment as Usual (ETAU) and the CBT intervention, whereas patients in the control arm receive only ETAU. The ETAU treatment includes the Mental Health Gap Action Programme (mhGAP). In this model, TB health workers (TBHWs)—non-specialist healthcare providers already engaged in TB care and also called TB DOTS facilitators—are trained to deliver CBT sessions to TB patients diagnosed with depression. This approach allows for the efficient use of available resources and ensures that patients can access mental health care within their existing care pathways. Participants in the CONTROL intervention group will undergo six sessions of a CBT-based intervention; the content and modes of intervention were adapted based on the Southampton framework used previously in Pakistan [16]. The Southampton Adaptation Framework is utilized to culturally adapt CBT by considering a patient’s cultural background and religious affiliation, thereby enhancing mental health outcomes [17]. This framework concentrates on three main areas: awareness of culture and religion, assessment and engagement with cultural issues, and modifications in therapy to align with local values and norms [17]. CBT therapy aims at addressing depression while also employing problem-solving and motivational techniques to improve compliance with ATT. Each therapy session will be conducted one-on-one, lasting between 40 and 60 min [15]. The design and methodology of the CONTROL trial are detailed in its published protocol [15], while this paper focuses on the methodology used for the process evaluation of the CONTROL trial.

While RCTs are the gold standard for evaluating clinical outcomes and cost-effectiveness, they often fail to capture the underlying mechanisms determining intervention success or failure [18]. RCTs typically focus on clinical outcomes such as morbidity and intervention effectiveness, neglecting the contextual factors, implementation processes, and stakeholder experiences that influence these results [19]. The requirements to publish the methodology and protocols for the randomized controlled trials have helped the reporting and quality of RCTs over the last two decades. The same is not valid for the process evaluation. The process evaluation in clinical trials informs the key stages in implementing trial procedures and how these are implemented in the real world, which is rarely captured in the clinical trials reporting.

The limited reporting of trial processes and implementation in real-world settings reduces the generalizability and scalability of trial findings, particularly in complex health systems [20]. The UK Medical Research Council’s (MRC) framework for designing and evaluating complex interventions (programs) recommends process evaluations be undertaken as part of all randomized trials, as they describe important contextual factors and can clarify causal mechanisms to aid the interpretation of trial findings and explain variations in trial outcomes [20]. Process evaluations address this gap by systematically investigating how interventions are delivered, received, and sustained in real-world settings [21]. They provide insights into the “how” and “why” behind trial outcomes [22], enabling policymakers and practitioners to adapt and scale up successful interventions. Process evaluations are especially critical in hybrid trials like CONTROL, where effectiveness and implementation are key research components [20]. By measuring these outcomes, we can identify mechanisms and causal relationships in implementation processes, ultimately strengthening the evidence for effective implementation [23]. In this context, Proctor’s framework of implementation outcomes will guide the process evaluation of the CONTROL trial. This framework identifies eight key dimensions essential for understanding complex interventions’ implementation: acceptability, adoption, appropriateness, feasibility, fidelity, implementation cost, penetration, and sustainability [23].

The findings from the process evaluation will generate evidence to inform CONTROL’s adoption and scale-up within Pakistan’s TB control program by exploring the intervention’s contextual and operational dynamics. Moreover, the insights will contribute to the broader evidence on integrating mental health care into chronic disease management in LMICs, addressing a critical gap in global health research. This paper is a protocol for a trial’s process evaluation, aiming to capture the multifaceted implementation aspects and identify actionable strategies for the scale-up of the intervention. The specific objectives of the process evaluation of the CONTROL trial are to:Describe the acceptability, appropriateness, adoption, and feasibility of the CONTROL study and CBT intervention within the routine TB control program of KP Pakistan.Describe the fidelity to CONTROL CBT intervention delivery.Describe the penetration, sustainability, and implementation costs of the mental health assessment measures and CBT therapy within the routine TB control program of KP Pakistan.Explore the barriers and facilitators to the sustainability and scale-up of CBT therapy within KP Pakistan's routine TB control program.

## Methods

This protocol provides a detailed methodology for the comprehensive process evaluation of the CONTROL study. Employing quantitative and qualitative methods, the evaluation will examine the practical challenges, contextual alignment, and effectiveness of the intervention within a TB care setting [24].

### Study design and settings

Through a concurrent mixed-method approach using quantitative and qualitative methods, we will comprehensively evaluate key implementation outcomes defined by Proctor’s framework (Table 2) [23]. The CONTROL CBT intervention will be delivered over nine months at 12 purposively selected TB care facilities (Study centers) at two study sites, districts Peshawar and Haripur, located in Khyber Pakhtunkhwa, Pakistan [15]. The selected facilities represent a mix of primary, secondary, and tertiary care settings, ensuring the intervention’s applicability and evaluation across various healthcare system levels.

Although extensively trained before the pilot phase of the trial, the TBHWs will undergo a “ten-day training course” designed to help them understand the core principles of CBT, acquire practical techniques for managing depression and anxiety in TB, and enhance their communication skills. In these trainings, master trainers, initially trained by a team comprising senior psychiatrists and a psychologist with extensive expertise in CBT delivery, will subsequently train the TBHWs to implement the intervention [15]. Medical officers (MOs) responsible for treating TB patients at each facility will receive training in the Mental Health Gap Action Programme (mhGAP). The MOs will deliver mhGAP, as enhanced treatment as usual (ETAU), to both arms of TB patients. The mhGAP training for the MOs will be delivered by a psychiatrist. This training will be based on the World Health Organization’s mhGAP intervention guide [25], ensuring alignment with standardized global mental health guidelines [15]. After each training session, participant feedback will be systematically collected to evaluate satisfaction levels. A feedback form, translated into Urdu for cultural and linguistic appropriateness, will be utilized.

### Data collection

Several quantitative and qualitative approaches will be used to gather insights from TB patients, TBHWs, medical officers, the trial team, and TB program managers. Tables 2 and 3 outline these methods and their respective participants. Table 1, mentioned below, represents the scheduled timing of all data collection tools during the trial. We first explain the details of the quantitative methods for the first three objectives of the study. We then explain the qualitative methods overall and specifically for objective 4 of the study.

**Table 1 Tab1:**
[figure not shown]
Schedule of the CONTROL intervention process evaluation data collection methods

### Quantitative data

Quantitative data collection for the process evaluation will systematically measure key implementation outcomes related to integrating mental health screening and CBT therapy within the routine TB control program in KP, Pakistan. Data will be collected using routine trial logs (Excel sheets consisting of prescreening, screening, recruitment data, retention data, and CBT records), structured checklists and questionnaires, patient records, and fidelity assessment tools.

## Acceptability, appropriateness, adoption and feasibility

Four quantitative tools will collect data on Proctor et al.’s four implementation outcomes: acceptability, appropriateness, adoption, and feasibility [23].

### Data collection tools

Acceptability, appropriateness, and feasibility of the CONTROL study and CBT intervention will be assessed at 8 weeks post-randomization using three valid and reliable scales developed by Weiner et al., the Acceptability of Intervention Measure (AIM), Intervention Appropriateness Measure (IAM), and the Feasibility of Intervention Measure (FIM) [26]. For sampling, measuring tools, and data collection time points, see Table 2. Each scale consists of four thematic questions with five responses ranging from “completely disagree” to “completely agree” on a five-point Likert scale [27]. Selected for their conceptual distinctiveness, AIM, IAM, and FIM provide valuable insights into the implementation process while also accounting for potential empirical interrelations [27]. They enhance the evaluation by providing robust, evidence-based metrics to assess the feasibility and acceptability of the intervention in complex healthcare settings [27].

**Table 2 Tab2:** Implementation outcomes for CONTROL trial process evaluation

Quantitative measures					
**Sr. No**	**Outcomes**	**Brief description**	**Measuring tool**	**Data collection timepoint**	**Group (patients, therapist, trial team)**
**1**	**Appropriateness**	Appropriateness refers to the perceived fit, relevance, compatibility, suitability, usefulness, and practicability of the CBT intervention within the TB care settings, as experienced by facilitators and participants	Intervention Appropriateness Measure (IAM)	8-week	10% of randomly selected patients in the intervention arm
			The Applied Mental Health Research Group (AMHR)-appropriateness subscale	8-week	10% of randomly selected patients in the intervention arm
**2**	**Feasibility**	The CBT intervention’s actual fit, utility, and practicability within routine TB care, assessing the extent to which TBHWs can effectively deliver CBT and patients can access and engage with it given the available resources, time, and training	Feasibility of Intervention Measure (FIM)	32-week	All trial staff (DOTS and the trial team)
			The Applied Mental Health Research Group (AMHR)- feasibility subscale	8-week	10% of randomly selected patients in the intervention arm
			% assigned to the intervention who agreed to enroll in the trial	After the definitive trial, all relevant data will be retrieved from the trial team’s data logs	
**3**	**Adoption**	Adoption refers to the early uptake, utilization, and initial implementation of the CBT intervention within The CONTROL Trial and their intention to integrate it into routine TB care	The Applied Mental Health Research Group (AMHR)-adoption subscale	8-week	10% of randomly selected patients in the intervention arm
**4**	**Acceptability**	Acceptability refers to participants' satisfaction and perceptions regarding various aspects of the CBT intervention delivered under The CONTROL Trial, including its content, complexity, ease of participation, delivery method, and perceived credibility	The Applied Mental Health Research Group (AMHR)-acceptability subscale	8-week	10% of randomly selected patients in the intervention arm
			Acceptability of Intervention Measure (AIM)	8-week	10% of randomly selected patients in the intervention arm
			Retention in the number of sessions attended and % of those who dropped out of the intervention	After the definitive trial, all relevant data will be retrieved from the trial team's data logs	
**5**	**Fidelity**	The extent to which the CBT intervention is delivered as intended, ensuring adherence to the structured protocol, maintaining integrity in session delivery, and upholding the quality of program implementation by TBHWs within routine TB care	The Revised Cognitive Therapy Scale (CTS-R)	Ongoing process (first to sixth week post-randomization)	10% of all the sessions, delivered by the DOTS facilitator
			CBT content delivery assessment scale		
**6**	**Penetration**	The extent to which the CBT intervention is institutionalized within the TB care system, assessing its spread across healthcare facilities and the level of service access for TB patients needing psychological support	Data from the routine trial logs	After the definitive trial, all relevant data will be retrieved from the trial team’s data logs	
**7**	**Sustainability**	The extent to which the CBT intervention is maintained, continued, and durably integrated into routine TB care beyond the CONTROL trial, assessing its incorporation into health system structures, institutionalization within policies, and sustained use by TBHWs and patients	Administrative Data logs	After the definitive trial, all relevant data will be retrieved from the trial team’s data logs	
**8**	**Implementation Cost**	The financial investment required to deliver the CBT intervention within routine TB care, considering marginal costs, cost-effectiveness, and cost–benefit concerning its scalability and sustainability	Administrative Data logs	After the definitive trial, all relevant data will be retrieved from the trial team’s data logs	

The Applied Mental Health Research Group (AMHR) developed a comprehensive measure to evaluate multiple implementation domains, encompassing four constructs: acceptability (17 items), appropriateness (13 items), feasibility (14 items), and adoption (8 items). Each construct is assessed using a four-point Likert scale, with response options ranging from 0 “Not at all” to 3 “A lot” [28]. The AMHR tool is a validated instrument explicitly designed to allow adaptation to specific interventions.

We will use the AMHR tool for triangulation and to strengthen the findings on the four implementation outcomes. The AMHR will be culturally adapted to ensure cultural and contextual relevance. This will include the expert validity via online Google Forms. The experts include public health professionals, psychiatrists, CBT specialists, psychologists, and medical education experts. The experts will evaluate each item for relevance, clarity, and importance. Based on the three domains, a Content Validity Index (CVI) will be calculated for their responses to assess and confirm the tool’s appropriateness and cultural adaptability for the target population. It is recommended that a scale demonstrates excellent content validity with I-CVI values of 0.78 or above and S-CVI/Ave values of 0.9 or higher [29–31].

### Data collection and sampling

The above quantitative measures will be applied to collect data from the intervention group. The process evaluation will involve a carefully selected population from various groups, including patients, CBT therapists (TBHWs), and trial staff, to ensure comprehensive representation and validity of findings.

Data collection from all TBHWs and trial staff will utilize FIM. Research assistants from the process evaluation team will facilitate the completion of the tool by TBHWs and trial staff at the 32-week post-randomization mark, ensuring standardized and accurate data collection. The IAM and AIM will assess 10% of patients who have completed therapy sessions. Data collection will occur 8 weeks after randomization by the research assistants. The tools (FIM, IAM, AIM) will be translated into the local language to ensure cultural and linguistic relevance.

The AMHR subscales for appropriateness, adoption, feasibility, and acceptability will be administered to 10% of randomly selected patients in the intervention arm at 8 weeks post-randomization. The AMHR tool will be updated based on the CVI results and subsequently translated into the local language.

Retention rates, encompassing the number of sessions attended and the proportion of participants who discontinued the intervention, will be systematically evaluated [15]. Furthermore, the enrollment rate, defined as the percentage of individuals assigned to the intervention who consented to participate, will also be analyzed. These data will be extracted from the trial logs upon the completion of the definitive trial, offering valuable insights into participant engagement, adherence, and overall intervention feasibility and acceptability [15].

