### Data collection and sampling

A comprehensive sampling strategy will include a wide range of insights and diverse perspectives targeting key stakeholder groups, providing an in-depth understanding of the implementation process and factors influencing the intervention's scalability. Patients who completed the intervention (attended five or all six sessions) will be sampled to conduct 10–15 SSIs at 8 weeks post-randomization, while patients who partially completed the intervention (attended 1–4 sessions) will contribute 5–10 SSIs in the same timeframe (Table 3). From a policy-level perspective, 8–12 SSIs will be conducted with TB control program managers, health administrators, pulmonology health care workers from private practice, and infectious disease program managers after the final CBT session delivery to all trial intervention arm patients. Moreover, 5–10 SSIs will be conducted with control arm patients after 24 weeks post-randomization to capture their perspectives. We will also conduct seven FGDs after 24 weeks post-randomization with TBHWs (*n* = 2), CONTROL trial staff (*n* = 3), and TB program medical officers (*n* = 2).

**Table 3 Tab3:** Qualitative data collection using topic guides based on Proctor et al.’s implementation outcomes and exploring barriers and facilitators to future scale-up

Qualitative measures			
**Group of participants**	**SSIs**	**FGDs**	**Timeline**
Patients who completed the intervention (attended five or all six sessions), the maximum variation	10–15	Nil	After 8 weeks post-randomization
Patients who couldn’t complete the intervention (attended 1–4 sessions)	5–10	Nil	After 8 weeks post-randomization
Patients in the control arm	5–10	Nil	After 24 weeks post-randomization
DOTS facilitators		02	After 24 weeks post-randomization
Medical officers		02	After 24 weeks post-randomization
Trial staff		03	After 24 weeks post-randomization
TB control program management, (ii) health administrators, (iii) TB and Pulmonology health care workers diagnosing and treating TB in private practice, and (iv) the managers of the infectious disease program	8–12	Nil	After the delivery of the final session to all the trial participants
Total	30–35	07	

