## Data analysis

### Quantitative data analysis

We will employ descriptive and inferential statistical methods to analyse the CONTROL study and CBT intervention’s implementation outcomes—acceptability, appropriateness, adoption, and feasibility. Data from the AIM, IAM, FIM, and AMHR scales will be analysed to assess central tendencies and variability. Regression analyses will be conducted to explore relationships between implementation outcomes and participant characteristics. Retention and enrolment rates will be calculated as proportions, with chi-square tests to examine group differences.

Two independent reviewers, both experts in CBT, will assess a randomized selection of 10% of the audio-recorded CBT sessions to analyse the fidelity of the CONTROL CBT intervention through CTS-R and a CBT delivery assessment checklist. According to the Newcastle Cognitive Therapy Centre, a minimum competence standard is set at 36, with higher scores indicating greater therapeutic competence. Descriptive statistics will summarize the distribution of scores across sessions, and inter-rater reliability will be assessed using intraclass correlation coefficients to ensure consistency between reviewers. Similarly, the delivery assessment checklist evaluates adherence to the intervention’s content, and for each session, item scores will be aggregated to produce a total adherence score. Descriptive statistics will describe the adherence levels, and inter-rater reliability will be calculated to confirm reviewer consistency.

Penetration analysis will calculate the proportion of TB patients screened with the PHQ-2 and those referred for mental health services. High screening and referral rates will indicate successful penetration of mental health assessments into the TB program. Cost analysis will utilize data from the CSRI to compute the total and per-patient costs of implementing the mental health interventions. This will include direct costs (e.g., training, therapy sessions) and indirect costs (e.g., patient travel, lost productivity). The cost-effectiveness of the intervention will be evaluated by comparing the incremental costs to the health outcomes achieved, such as reductions in depression and anxiety symptoms.

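### The text samples AIM and IAM from therapy completers, Table 2 samples them from the whole intervention arm, and nothing reconciles the two

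*Protocol article*

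**What the plan says.** All of this stands in the Protocol article, under *Acceptability, appropriateness, adoption and feasibility*.

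- The *Data collection tools* text sends the reader to one place for the sampling rule: "For sampling, measuring tools, and data collection time points, see Table 2".
- Table 2, in the IAM row (appropriateness) and again in the AIM row (acceptability), names the group as "10% of randomly selected patients in the intervention arm", at 8 weeks. It sets no condition on completion.
- The *Data collection and sampling* text says instead: "The IAM and AIM will assess 10% of patients who have completed therapy sessions". It sets the same 8-week time, does not mention random selection, and does not say what counts as completion.
- The next paragraph of that text keeps the whole-arm rule for the AMHR subscales, which "will be administered to 10% of randomly selected patients in the intervention arm at 8 weeks post-randomization".
- The purpose of AMHR is stated as: "We will use the AMHR tool for triangulation and to strengthen the findings on the four implementation outcomes".

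Completion is defined only for the interviews, under *Qualitative data*: "Patients who completed the intervention (attended five or all six sessions) will be sampled". Patients who attended one to four sessions form a separate interview group there.

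**The concern.** The two rules select different patients, and field staff cannot follow both. The choice matters because of what these scales measure. Patients who found the therapy unacceptable or unsuitable are the ones one would expect to stop. Table 2 makes the same link by listing session attendance and the percentage who dropped out as measures of acceptability. A completers-only sample therefore selects on an indicator of the construct being measured.

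It also weakens the comparison between instruments. AMHR is there to corroborate AIM and IAM on the same outcomes. If AIM and IAM describe completers while AMHR describes the whole arm, neither agreement nor disagreement between them can be read cleanly.

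Acceptability and appropriateness belong to the first objective, and the findings are meant to inform adoption and scale-up. A patient who was not approached at 8 weeks cannot be recovered at the analysis stage.

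**Working it through.** **Size of the sample.** The article gives no number for AIM and IAM. Its only patient-level 10% sample with a number is the fidelity sample: 35 participant IDs for each of six sessions, and 35 × 6 = 210 recordings, as stated. If 35 is 10%, the intervention arm is 35 / 0.10 = 350 patients. Table 2 then implies about 35 patients for AIM and IAM.

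**Bias of a completers-only mean.** Let c be the completion rate, M_C the mean score in completers and M_N the mean in non-completers.

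- Arm mean = c × M_C + (1 − c) × M_N
- Completer mean minus arm mean = (1 − c) × (M_C − M_N)

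The documents give no value for c or for either mean. The values of c, the score differences of 0.5 and 1.0, the 1–5 scoring of the five-point items and the SD of 0.8 are assumptions. The completer sample is 10% of 350 × c. Its standard error is 0.8 / √n, without a finite-population correction.

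| Completion c | Completer sample n | Non-completers expected in a random 35, 35 × (1 − c) | Bias, difference 0.5 | Bias, difference 1.0 | Standard error of completer mean |
|---|---|---|---|---|---|
| 90% | 31.5 | 3.5 | 0.05 | 0.10 | 0.14 |
| 80% | 28.0 | 7.0 | 0.10 | 0.20 | 0.15 |
| 70% | 24.5 | 10.5 | 0.15 | 0.30 | 0.16 |
| 60% | 21.0 | 14.0 | 0.20 | 0.40 | 0.17 |

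For example, at c = 80% and a difference of 1.0, the bias is 0.20 × 1.0 = 0.20 and the standard error is 0.8 / √28 = 0.15.

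**Reading the table.** With a difference of 1.0 point, the bias exceeds one standard error at 80% completion and below. With a difference of 0.5, it does so only at 60%. At 90% completion it stays below one standard error in both columns, and it goes to zero as c approaches 100%.

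**Comparison with AMHR.** AMHR is drawn from the whole arm, so the same (1 − c) × (M_C − M_N) would sit between a completers-only AIM or IAM result and an AMHR result even if the instruments agreed perfectly within each patient. AMHR items are scored 0–3, so the amount does not carry over in points; the mechanism does.

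**The case against.** The strongest reply has four parts.

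**The document already points to the better rule.** Table 2 is named as the source for sampling, and the sampling text opens by applying the measures to the intervention group. The phrase about completed sessions might mean only that the therapy period is over by week 8. That is possible, but the text does not say so. The adjacent AMHR paragraph uses different wording, and elsewhere the article uses completion to mean five or six sessions. The conflict remains, though the repair is one sentence.

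**The bias is not demonstrated.** A reader might infer that the scores will be overstated. The documents do not support that as a certainty: they give no completion rate and no scores by attendance. The upward direction is the expected one, but it is an inference, and the size rests wholly on assumptions. This part stands.

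**Other evidence on non-completers is planned.** AMHR covers acceptability and appropriateness in the whole arm, attendance and dropout are analysed from the trial logs, and 5–10 interviews are planned with patients who attended one to four sessions. This limits the harm, but does not make AIM and IAM scores from completers apply to the arm.

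**Two wider criticisms do not follow.** A reader might infer that the sample is unstratified across the 12 facilities. The article is silent on this, and a condensed article may leave it to the full protocol. A reader might also set the abstract's "Quantitative data will be analyzed descriptively" against "Regression analyses will be conducted to explore relationships between implementation outcomes and participant characteristics" and conclude that the regressions should be dropped as too small. The regressions are exploratory and are not confined to AIM and IAM; retention, which Table 2 lists under acceptability, covers the whole arm.

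**Conclusion.** The contradiction is explicit in the current text and needs no assumption. Under the completer rule, AIM and IAM would probably be too favourable as a description of the whole arm. The illustrative size is 0.05–0.40 points on a 1–5 scale, assuming 10–40% non-completion and a 0.5–1.0 point difference, and near zero if almost all patients complete. The comparison with AMHR would be confounded by the difference in sampling frame. Under the Table 2 rule this selection does not arise, provided the sampled patients who stopped are reached. The point is confined to AIM and IAM sampling in a process evaluation; it does not touch the trial's clinical outcomes.

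**What to change.** Change the AIM and IAM sentence under *Data collection and sampling* to match Table 2: both scales, like AMHR, go to a random 10% of the intervention arm at 8 weeks, regardless of the number of sessions attended. Report the number of sessions attended and the response rate among those sampled, so that a shortfall among patients who stopped is visible.

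If completers really are the intended group, Table 2 would have to change instead, completion would need a definition for this purpose, and the results should be labelled as applying to completers only. The mismatch with AMHR would then remain.

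The cost is protocol wording plus some harder contacts: on the figures above, about 4 to 14 of 35 sampled patients would be non-completers at 90–60% completion. Some who attended few or no sessions may be unable to rate the content, which the response rate would show. Mean scores may come out slightly lower.
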